#### Treatment of adverse events

6.5.2

If there are adverse reactions in the process of acupuncture, it is necessary to deal with them timely and properly until the patient's condition is stable. Those with abnormal laboratory tests will be tracked until they return to normal. Researchers will need to analyze whether the adverse events are related to the trial interventions, and decide whether to discontinue the trial based on the severity of the adverse events. For those with serious adverse reactions, relevant departments will be consulted immediately. And we will report to the ethics committee in the first time (within 2 hours).

## Quality control and assurance

7

This study will control bias from the following aspects to improve the quality of research.

1.The participants will come from hospitals and surrounding communities to avoid hospital selection bias.2.Acupuncture treatment, blood pressure measurement, and acupoint diagnosis will be operated by 3 doctors respectively (each item will operated by the same doctor), so as to avoid bias caused by doctors with different qualifications.3.To reduce the measurement bias, the blood pressure measuring instrument recommended in Chinese guidelines for the prevention and treatment of hypertension (revised version 2018) will be used.4.The data analysis team will be entrusted to analyze the data, and the research group will publish the real and complete results to eliminate the publication bias.

## Data management

8

All information related with this trial will be recorded in CRFs by a trained and qualified investigator. No correction of completed CRFs is allowed once completed. The record of CRFs will be reviewed by the clinical inspector. To ensure the accuracy of the data, 2 investigators will input and proofread the data respectively. In addition, all papery documents and electronic versions of the CRF will be preserved in the secure research archives for 5 years after trial completing at the Dongzhimen Hospital Affiliated to Beijing University of Chinese Medicine and only can be viewed by the research team.

## Statistical analysis

9

SPSS 20.0 statistical software will be used for data statistics (SPSS Inc, Chicago, IL). The frequency percentage will be used to describe the demographic data. For the measurement data with normal distribution and homogeneous variance, mean ± standard deviation (\bar{x} (Latex code) ± s) will used to describe the data. Paired and independent sample *t* test will used for intragroup and intergroup comparison respectively. For the measurement data of non-normal distribution, nonparametric test will be used. The blood pressure value will be analyzed by repeated measurement analysis of variance. In the correlation analysis of 2 theoretically related continuous variables, Pearson correlation coefficient model will be used if the data meet the normal distribution, and Spearman correlation coefficient model will be used if the data are nonnormal distribution. *χ*^2^ test will be used for counting data. All tests will be bilateral; *P* < .05 means the difference is statistically significant. In the correlation analysis, 0 < R≤0.2 means that there is no correlation between variables; 0.2<R≤0.4 means that there is a low correlation between variables; 0.4<R≤0.8 means that there is a moderate correlation between variables; 0.8 < R≤1 means that there is a high correlation between variables.

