### Inclusion criteria

3.3

1.Age: 18 to 65 years, both male and female;2.Met the Western diagnostic criteria of essential hypertension. For patients without antihypertensive drugs, SBP: 140 to 179 mmHg and/or DBP: 90 to 109 mmHg. For patients with antihypertensive drugs, hypertension should be stabilized at a normal high value. The patients who took medicine used ≤2 antihypertensive drugs for >2 months.3.Confirmed TCM diagnosis of HLY in hypertension.4.Not receives acupuncture or Chinese herbal medicine treatment in recent 1 month.5.Good compliance with the observation and evaluation of researchers.6.Informed consent is signed by the patient himself or his immediate family members.

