### Main outcome

6.1

Ambulatory blood pressure monitoring: 24 hours ambulatory blood pressure is the “criterion standard” to evaluate the antihypertensive effect.^[11]^ In this study, the 24 hours ambulatory blood pressure monitor (DMS-ABP) made by American Tim will be used for data collection. Ambulatory blood pressure will be measured in patients’ nondominant arm to reduce the impact of activity on blood pressure measurement. The detection time of each patient should be >23 hours. At the same time, the effective reading is >70%. There are at least 20 daytime blood pressure readings and 6 nighttime blood pressure readings.

Ambulatory blood pressure monitoring will be evaluated in the first week (baseline period), the fifth week (after acupuncture period), and the seventh week (after follow-up period).

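### Blood pressure is assigned to repeated-measures ANOVA and t tests with no baseline covariate and no deciding contrast; a baseline-adjusted model would be more precise and give a direct effect estimate

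*Protocol article*

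**What the plan says.** Section 9 (Statistical analysis) gives blood pressure its own sentence: "The blood pressure value will be analyzed by repeated measurement analysis of variance". For normally distributed measurement data in general it says: "Paired and independent sample *t* test will used for intragroup and intergroup comparison respectively". It adds: "All tests will be bilateral", with significance at P below .05. It names no covariate, no change score and no deciding ANOVA effect.

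Section 6.1 (Main outcome) sets the visits for the primary outcome: "Ambulatory blood pressure monitoring will be evaluated in the first week (baseline period), the fifth week (after acupuncture period), and the seventh week". Baseline is therefore one of the three measurements.

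Section 3.3 (Inclusion criteria) admits untreated patients with systolic pressure of 140 to 179 mmHg and/or diastolic pressure of 90 to 109 mmHg. It also admits patients on drugs, for whom "hypertension should be stabilized at a normal high value". Section 3.5.2 promises an intention analysis and counts patients with more than half the treatment course in the efficacy analysis. Section 4.2 expects 20% shedding.

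**The concern.** A repeated-measures ANOVA of three visits has two effects that could be read as the treatment result. The group main effect averages the arm difference over all visits, including baseline, where randomisation makes the expected difference zero. The group-by-time interaction asks whether the arms change differently, but as a 2-df test it does not say by how much or in which direction. Neither uses baseline as efficiently as a covariate does. Baseline is likely to be prognostic here because eligibility mixes untreated and drug-controlled patients.

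The classical procedure also needs every visit from every patient. Someone who had most of the treatment but missed week 7 falls out, which sits badly with sections 3.5.2 and 4.2.

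Paired tests within an arm are not randomised comparisons. Untreated patients are selected for raised pressure, so some fall by regression to the mean is expected in both arms. A significant fall in one arm only could then be mistaken for a treatment effect.

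**Working it through.** **Inputs from the protocol article.** Three visits including baseline (6.1); 1:1 allocation (2.1); two-sided 0.05 (9); 23 per arm before shedding, 56 in total (4.2). The total reproduces: 23 × 1.2 = 27.6, rounded up to 28 per arm, so 56. The 22.57 behind the 23 cannot be recomputed from the article, because it gives no margin, SD or power.

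**Assumptions, not in the article.** Equal correlation ρ between visits, 0.6 with a range of 0.3 to 0.8. The week-5 effect is d = 0.845 SD, chosen because it gives a week-5 t test 80% power at 23 per arm. The effect is fully sustained at week 7 unless stated otherwise.

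**Formulas.** For the t-type tests, the noncentrality is the standardised effect × √(n/2), and √(23/2) = 3.391.

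- t test at week 5: 0.845 × 3.391 = 2.866 on 44 df; power 80.0%.
- Group main effect: the mean difference is (0 + d + d)/3 = 0.563, and the SD of a patient's three-visit mean is √((1 + 2ρ)/3) = √(2.2/3) = 0.856. The ratio is 0.658 and the noncentrality 2.231; power 58.8%.
- Interaction: λ = n × SS / (2(1 − ρ)), where SS is the sum of squared deviations of (0, d, d) from their mean, (2/3)d² = 0.476. So λ = 23 × 0.476 / 0.8 = 13.7 on 2 and 88 df; power 91%.
- Week-5 ANCOVA: d/√(1 − ρ²) = 0.845/0.8 = 1.056; noncentrality 3.582 on 43 df; power 93.8%.
- ANCOVA on the mean of weeks 5 and 7: residual variance (1 + ρ)/2 − ρ² = 0.44; power 99%.

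**Range over ρ, effect sustained.**

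| Test | ρ 0.3 | 0.5 | 0.6 | 0.7 | 0.8 |
|---|---|---|---|---|---|
| t test at week 5 | 80% | 80% | 80% | 80% | 80% |
| Group main effect | 73% | 63% | 59% | 55% | 52% |
| Interaction | 69% | 84% | 91% | 97.2% | 99.8% |
| Week-5 ANCOVA | 84% | 90% | 94% | 97.5% | 99.7% |

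**If the effect fades by week 7 (ρ = 0.6).** The main-effect numerator becomes d/2 if half is lost and d/3 if all is lost, giving 37% and 19% power. The interaction gives 81% and 91%. Week-5 ANCOVA stays at 94%.

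**Sensitivity.** With d = 0.826 (80% power by the normal approximation), the main effect runs from 71% to 50% and week-5 ANCOVA from 82% to 99.5% over the same range of ρ. Using 28 per arm, with the effect rescaled to 0.749 SD, changes the powers by less than 0.01.

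**Paired tests with no treatment difference.** Suppose both arms drift by 0.5 SD of the change. The noncentrality is 0.5 × √23 = 2.40 on 22 df, so each arm is significant with probability 0.63. Exactly one arm is significant in 2 × 0.63 × 0.37 = 47% of trials, and the acupuncture arm alone in 0.63 × 0.37 = 23%.

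**The case against.** The strongest reply is that the interaction is the usual treatment test in this design. It contrasts changes from baseline between arms and so removes baseline differences. With ρ at 0.7 or more and a sustained effect it practically equals week-5 ANCOVA. The mixed eligibility may itself push ρ up. This stands, and it rules out a reading that a reader might reach: that none of the named analyses takes account of baseline. The large losses (59%, 37%, 19%) arise only if the main effect is read as the result, and the article does not say that it will be.

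Three further inferences are tempting but not stated. That baseline is a level of the ANOVA follows naturally from the three visits, but section 9 does not say so. That the independent t test uses raw follow-up values is not stated either; changes remain possible. And because blood pressure has its own sentence, the t tests may be meant only for scales such as HAD and the syndrome score. Nor does the article say that within-group P values will serve as evidence of efficacy; that harm depends on how they are read.

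It is also fair that a condensed article may leave covariates, the deciding contrast and missing visits to a fuller plan. Silence on these is not the fault raised. The article does name a method, however, and a fuller plan would have to replace that method to gain the precision that the baseline recording offers.

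**Conclusion.** The point holds in limited form and should be fixed. The named between-group tests are valid: in a randomised comparison they do not inflate type I error, and a reader should not infer a biased trial. The cost is precision and the lack of a direct treatment estimate.

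If baseline is a level and the main effect is read, the effect is diluted to two thirds at best, with power of 73% to 52% over ρ 0.3 to 0.8, against 84% to 99.7% for week-5 ANCOVA. If the interaction is read, the loss is negligible at ρ of 0.7 or more with a sustained effect, but material at lower ρ (69% against 84% at 0.3). Under either reading, the classical method drops patients who miss a visit. All powers rest on the assumed effect, equal correlation between visits and 23 per arm; the article gives neither the effect nor ρ.

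**What to change.** Make the between-group comparison of 24-hour ambulatory pressure an ANCOVA with baseline 24-hour pressure as covariate, or a mixed model of weeks 5 and 7 with the same covariate. Drug status at entry can be added. The mixed model also keeps a patient who has only one of the two follow-up visits. The sponsor should name the deciding pressure component and time point before data are seen.

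Report the adjusted difference between arms with its 95% CI. An interval is also what the non-inferiority aim in section 4.2 would need. Use the same form for clinic pressure, HAD and the syndrome score. Keep paired within-group changes as description, not as evidence of efficacy.

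The cost is wording in the analysis section. No new data or visits are needed, and the named software can fit both models.

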### Estimation of sample size

4.2

The purpose of this study is to observe that the antihypertensive effect of acupuncture combined with medicine is not inferior to that of Western medicine alone. Therefore, the sample calculation is based on the sample content calculation formula of noninferiority test.^[8]^ The calculation result is 22.57, that is, the experimental group and the control group need about 23 patients, respectively. According to the shedding rate of 20%, a total of 56 patients will be recruited.

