### Auxiliary outcomes

6.3

1.Blood pressure load: blood pressure load is the percentage of times that SBP and DBP readings exceed the normal range respectively. The normal standard is 24- hour ambulatory blood pressure <130/80 mmHg, daytime blood pressure <135/85 mmHg, and nighttime blood pressure <120/70 mmHg. It is generally considered that normal load should be <5%.2.Risk rate of salt sensitivity: In 2011, Italian scholars proposed that the risk rate of salt sensitivity can be preliminarily determined by the nighttime blood pressure drop rate (monitored by 24-hour ambulatory blood pressure) combined with 24-hour average heart rate.^[12]^ The specific assessment method: the blood pressure of the observed patients does not drop at night, that is, the patients with nondipper blood pressure. If their 24-hour heart rate is ≥70 beats/min, about 70% of them are salt sensitive in the saline infusion test, and define this type of patients as having high risk of salt sensitivity. Dipper blood pressure and 24-hour heart rate <70 beats/min are defined as low risk of salt sensitivity, whereas others are defined as medium risk of salt sensitivity.

The auxiliary outcomes mentioned above will be evaluated at the first week (baseline period) and the fifth week (after acupuncture period).

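### The three ordered salt-sensitivity classes appear to fall under a chi-square test that ignores their order; a rank or proportional-odds analysis would usually be somewhat more sensitive

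*Protocol article*

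**What the plan says.** Section 6.3 (Auxiliary outcomes) builds the outcome from night-time dipping and 24-hour heart rate. For non-dippers with a heart rate of at least 70 beats/min, the authors "define this type of patients as having high risk of salt sensitivity". Dippers with a heart rate below 70 "are defined as low risk of salt sensitivity, whereas others are defined as medium risk of salt sensitivity". Timing is given for the whole tier: "The auxiliary outcomes mentioned above will be evaluated at the first week (baseline period) and the fifth week (after acupuncture period").

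Section 9 (Statistical analysis) assigns tests by type of data:

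- Normal measurement data: paired and independent t tests.
- Other measurement data: "For the measurement data of non-normal distribution, nonparametric test will be used".
- Blood pressure: repeated-measures analysis of variance.
- Categorical data: the chi-square "test will be used for counting data".

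On sidedness: "All tests will be bilateral", with P below 0.05 as the threshold. Section 9 does not mention the salt-sensitivity classes and gives no rule for ordered categories.

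**The concern.** Low, medium and high have a natural order, and the question of interest is directional: does risk move down when acupuncture is added? The ordinary chi-square test on a two-arm by three-class table has 2 degrees of freedom and gives the same P value however the three classes are relabelled. It spreads its sensitivity over every pattern of difference. Two consequences follow. A real downward shift is more likely to be missed in a small trial, and a small P value need not mean lower risk, because emptying the medium class into both extremes also produces one. A comparison of week-5 counts alone would also make no use of the class recorded at week 1.

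**Working it through.** **Inputs from the article.** Three classes (section 6.3); two-sided 5% level (section 9); sample size (section 4.2): "the experimental group and the control group need about 23 patients, respectively", and "According to the shedding rate of 20%, a total of 56 patients will be recruited".

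**The article's own figure.** 22.57 rounds up to 23 per arm. Adding 20%: 23 × 1.20 = 27.6, rounded up to 28 per arm, and 2 × 28 = 56. This matches. So 23 per arm is the planned evaluable number and 28 the number with no dropout. The 22.57 itself cannot be rebuilt because its inputs are not given, and it was not derived for this outcome.

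**Which test applies.** A three-class label is not measurement data, so the t, nonparametric and repeated-measures rules do not reach it. Chi-square is the only listed test left. This is an inference.

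**Two invented tables, 23 per arm, low/medium/high.** With equal arms, chi-square = Σ 2(d/2)²/m, where d is the difference between the arms in a class and m the mean of the two counts.

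- Control 5/11/7 against acupuncture 11/9/3, a downward shift. Chi-square = 2(9/8) + 2(1/10) + 2(4/5) = 2.25 + 0.20 + 1.60 = 4.05, 2 df, P = 0.13. Tie-corrected rank-sum (no continuity correction): P = 0.047.
- Control 4/15/4 against 10/3/10, medium emptied equally both ways. Chi-square = 2(9/7) + 2(36/9) + 2(9/7) = 13.14, P = 0.0014. Rank-sum: P = 1.0.

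**Power simulation.** 100,000 trials per scenario compared Pearson chi-square with the tie-corrected Wilcoxon rank-sum test. The article gives no class frequencies, so five control splits were assumed (low/medium/high: equal thirds, 20/50/30, 10/50/40, 20/30/50, 30/50/20%). The shift was proportional: the odds of being at or below each class are multiplied by the odds ratio (OR).

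| OR | Chi-square vs rank-sum, 20/50/30, n = 23 | Same, n = 28 | Gain in points, all five splits, both n |
|---|---|---|---|
| 1.5 | 8.9% vs 10.9% | 9.9% vs 12.2% | about 2 |
| 2 | 17.6% vs 22.7% | 20.9% vs 27.0% | 5 to 6 |
| 3 | 38.3% vs 48.2% | 46.4% vs 56.8% | 9 to 11 |
| 4 | 57.1% vs 67.8% | 66.7% vs 76.3% | 9 to 12 |
| 5 | 70.4% vs 80.0% | 79.7% vs 87.1% | 7 to 11 |

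At OR 1 both tests reject in 4.3% to 5.1% of trials. As an analytic check, a noncentrality of 7.85 gives 80.0% power on 1 df and 70.9% on 2 df, a gap of 9 points.

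**Effect through dipping only.** Assume that dipping and heart rate are independent, with 40 to 60% of patients at 70 beats/min or more. Take half as the example.

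- Non-dipping falls from 60% to 40%. High goes from 0.6 × 0.5 = 30% to 20%, and low from 0.4 × 0.5 = 20% to 30%. The odds ratio is (0.30/0.70)/(0.20/0.80) = 1.71 at both cuts. Over the assumed range, power at 23 per arm is 12 to 13% against 15 to 16%, a gain of 3 to 4 points.
- Non-dipping halves from 60% to 30%. Odds ratios are about 2.0 to 2.6, and power is 23 to 24% against 30 to 31%, a gain of about 7 points (7 to 8 at 28 per arm).

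**Non-monotone shift.** Control 20/40/40 against 20/65/15 at 23 per arm: chi-square 41.9%, rank-sum 25.3%. Here the ranking of the tests reverses.

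**The case against.** The strongest reply is that section 9 is a short generic list in a condensed article. It says chi-square without specifying a 2-df Pearson test. A linear-trend chi-square would use the order, and the outcome's title, a risk rate, could also mean the proportion at high risk, for which a 2 × 2 chi-square is ordinary. The mapping of an auxiliary outcome to its test may be in the full protocol or analysis plan. This stands as far as it goes: the 2 × 3 test is an inference and is treated as one here. What remains is that the stated rule confines rank methods to measurement data and so, on its face, steers an ordered outcome to chi-square.

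A reader might infer a flat loss of about 10 points of power. The documents do not support that. They give no class distribution or effect size, and a loss of that size needs an assumed odds ratio of roughly 3 to 5. If acupuncture acts on dipping alone, even halving non-dipping does not reach that range, and both tests then have low power.

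A reader might also infer that chi-square is invalid, or that it hides direction. It holds its level, and class counts by arm would show which way patients moved. Nor is an unadjusted comparison wrong for leaving out week-1 class, since the arms are randomised. The rank-sum test leaves it out too.

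**Conclusion.** The point holds as a minor improvement in efficiency. The classes are ordered, and the only listed test that fits them does not use the order. Under proportional odds at 23 to 28 per arm, that costs about 2 points of power at an odds ratio of 1.5, 5 to 6 points at 2, and about 7 to 12 points at 3 to 5. For a dipping-only effect the cost is about 3 to 7 points at 23 per arm. These figures rest on assumed class splits and a one-directional shift. They compare chi-square with the rank-sum test; any further gain from adjusting for week-1 class was not quantified. The outcome is auxiliary, the trial is not sized for it, and neither the primary ambulatory blood pressure analysis nor the safety analysis is affected.

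**What to change.** In section 9, add that the ordered salt-sensitivity classes at week 5 are compared between arms by proportional-odds logistic regression with week-1 class as a covariate, reporting the common odds ratio with its confidence interval. Keep chi-square for unordered categories. A tie-corrected Wilcoxon rank-sum test is a simpler fallback, at the price of not using week-1 class.

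The cost is one sentence. Week-1 class is already collected, and both methods are available in SPSS 20.0, the software the article names. The downside is less sensitivity to changes that are not in one direction, such as patients leaving both extremes for the middle; class counts by arm would still show these.

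### The correlation bands call any R from 0 to 0.2 no correlation and give R ≤ 0 no class; at 56 patients or fewer the first label is not supported

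*Protocol article*

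**What the plan says.** Section 9 (Statistical analysis) plans correlation analysis for pairs of continuous variables that are related in theory. The variables are not named. The coefficient depends on the distribution: Pearson's for normal data; otherwise, "Spearman correlation coefficient model will be used if the data are nonnormal distribution".

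The result is then read from the value of R:

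- lowest band: "0 < R≤0.2 means that there is no correlation between variables"
- above 0.2 and up to 0.4: low
- above 0.4 and up to 0.8: moderate
- above 0.8 and up to 1: high

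No absolute-value sign appears, and the scale starts above 0. Just before the bands stands the general testing rule: "All tests will be bilateral", with the level set as P "< .05 means the difference is statistically significant". The text does not say how this rule and the bands work together.

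Section 4.2 (Estimation of sample size) plans 56 patients in total, from about 23 per group with 20% shedding. Section 2.1 sets 1:1 allocation.

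**The concern.** This is an interpretation rule that the protocol states, not a detail left for later. Applied literally, it does three things.

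1. It turns a small observed R into a statement that no correlation exists, although a sample of this size cannot separate zero from a moderate correlation.
2. It calls any R just above 0.2 a correlation, even where the data are compatible with none.
3. It leaves an inverse relation, however strong, without a class.

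At stake is how the correlation results will be worded in the report: absence claimed where the data are merely imprecise, and possibly presence claimed where there is only noise.

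**Working it through.** **Inputs.** The band limits 0.2, 0.4 and 0.8, and the two-sided 5% level, are from section 9. The total of 56, the 23 per group and the 20% shedding are from section 4.2.

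**The plan's own figure.** 23 × 1.2 = 27.6, rounded up to 28 per group, gives 56 in total. (Dividing by 0.8 instead gives 23/0.8 = 28.75, so 29 per group and 58; the difference is immaterial here.) The base figure 22.57 cannot be checked, because its inputs are not printed.

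**Assumed n.** The article does not say whether a correlation uses all patients or one group. The check therefore covers n = 56 (all recruited), 46 (2 × 23 evaluable), 28 (one group recruited) and 23 (one group evaluable).

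**Formulas.**

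- 95% interval (Fisher z): tanh(atanh(R) ± 1.96/√(n − 3)). It applies to Pearson and is approximate for Spearman.
- Smallest significant |R|: t/√(n − 2 + t²), with t the 97.5% point on n − 2 degrees of freedom.
- Chance of R ≤ 0.2 when the true correlation is 0.3: Φ[(atanh 0.2 − atanh 0.3) × √(n − 3)].
- Chance of |R| > 0.2 when the true correlation is 0: the two-sided P value of R = 0.20. Half of it is the chance of R > 0.2.

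**Example at n = 56.** atanh(0.2) = 0.2027 and 1.96/√53 = 0.2692. The limits are tanh(−0.0665) = −0.066 and tanh(0.4719) = 0.440. For a true correlation of 0.3: (0.2027 − 0.3095) × 7.280 = −0.78, and Φ(−0.78) = 0.218.

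| n | 95% CI at R = 0.20 | P at R = 0.20 | Smallest significant absolute R | R ≤ 0.2 if true value is 0.3 | R > 0.2 if true value is 0 | Absolute R > 0.2 if true value is 0 |
|---|---|---|---|---|---|---|
| 56 | −0.07 to 0.44 | 0.139 | 0.263 | 22% | 7% | 14% |
| 46 | −0.10 to 0.46 | 0.183 | 0.291 | 24% | 9% | 18% |
| 28 | −0.19 to 0.53 | 0.308 | 0.374 | 30% | 15% | 31% |
| 23 | −0.23 to 0.57 | 0.360 | 0.413 | 32% | 18% | 36% |

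**Reading the table.**

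- *Lowest band.* At every n, the interval at R = 0.20 covers zero and extends past 0.4 into the plan's moderate band. R = 0.20 would first reach P < .05 at n = 97.
- *Low band.* At n = 56, R = 0.25 has P = 0.063 and a 95% interval of −0.01 to 0.48, yet it carries the label of a low correlation. At n = 23 the non-significant range (up to 0.413) runs just into the moderate band.
- *Negative values.* At n = 56, R = −0.50 has a 95% interval of −0.67 to −0.27 and P < .001, and the printed scale has no class for it. If the true correlation is 0, about half of all results fall at R ≤ 0.

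**The case against.** **The P value governs significance and the bands only describe size.** This is a fair reading. The two-sided rule covers all tests, and the correlation tests are named in the same section. On that reading a low but non-significant R is no contradiction, since size and significance are different properties. A reader might infer that the bands conflict with the 5% rule. The text does not support that, because nowhere does a band override a non-significant P. What remains is that the P rule is worded for a difference and is not tied to the bands, and that the lowest band is worded as a conclusion about existence. Non-significance would not justify that wording either.

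**Strength bands are readily understood as applying to |R|.** Probably so, and then the gap for negative values is one of notation. But the choice affects the size of the problem. Read literally, only R > 0.2 is called a correlation, so the false-label rate is 7% at n = 56 and 15% at n = 28. The rates of 14% and 31% apply only if the bands mean |R|. A reader who complains that negative R has no class cannot also use the doubled rates.

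**The consequence is limited.** A reader might infer that the rule undermines the aim in the Discussion of linking acupoints with the internal organs. That is not established: section 9 names no variables, and section 6.4 (Exploratory indicators) does not say what the acupoint findings would be correlated with.

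**Conclusion.** The point holds as a minor one. The label for the lowest band is not supported at any plausible n. At n = 56, R = 0.20 is compatible with anything from −0.07 to 0.44, and a true correlation of 0.3 would fall at or below 0.2 in about 22% of trials (up to 32% with 23 patients). As printed, R ≤ 0 has no class. In the other direction, R between 0.20 and 0.263 at n = 56 would be called a low correlation without being significant.

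These figures assume n between 23 and 56, approximate normality of Fisher's z, and true correlations of 0 and 0.3 chosen for illustration. The primary outcome is 24-hour ambulatory blood pressure, and the blood pressure conclusions do not rest on the bands. Only secondary or exploratory correlation analyses are affected.

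**What to change.** Amend the closing sentence of section 9 so that:

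- the bands apply to |R| and the sign of R is reported;
- the lowest band is called very weak (or correlation not shown) instead of no correlation;
- the bands are said to describe strength only;
- evidence for a correlation is judged by the two-sided P value and the 95% confidence interval, both reported with R.

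A formal limit for declaring absence of correlation is more than this analysis needs. The cost is about one sentence and a routine interval calculation. No data collection or sample size changes, and the amendment should be made before the data are analysed.
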